### Detailed work plan

The instrumented assessment of wrist and finger spasticity will be analogous to clinical spasticity testing, capturing MAS and TS through slow and fast passive stretching of the muscle groups to be tested. During this process, sEMG signals and relevant joint angles will be measured using 3D motion analysis. Concurrently, subjective MAS and TS values will be recorded.

**Surface EMG and Motion Analysis**: sEMG signals and joint angles will be recorded during slow (30°/s) and fast (180°/s) passive stretching of the muscle groups [20]. A 5-second pause will be maintained between each repetition. The protocol includes the following passive stretches:Wrist extension with a clenched fist (particularly targeting FCU, FCR)Wrist extension with open fingers (targeting FDS, FDP, FCU, FCR)Thumb extension with the wrist in a neutral position (targeting FPL)**Measurement Procedure**: Stretching will be performed manually to ensure clinical applicability. Measurements will be taken with a metronome to maintain speed consistency and include inter-rater reliability testing.**Musculoskeletal Modeling**: A musculoskeletal model generated from 3D motion analysis will be applied to predict postoperative outcomes based on preoperative measurements. Specifically, this involves using preoperative experimental data from the patient and an individually scaled musculoskeletal model, into which the planned surgical procedure (e.g., muscle-tendon lengthening) is incorporated. This allows for the simulation of potential surgical outcomes, such as changes in joint range of motion or the patient’s ability to generate functional movement. For musculoskeletal modeling, the dynamic upper extremity model developed by Saul and Holzbaur [21] was selected due to its high level of anatomical detail, ranging from the thorax to the wrist. The model includes 22 segments and 15 degrees of freedom. Additionally, it represents 32 muscles using 50 Hill-type muscle-tendon actuators. Forward dynamics simulations will be conducted using EMG data as input.**Measurement Time Points** (Fig 1):**HEALTHY PARTICIPANTS:** Two measurements, 7 days apart (***t***_***1***_***, t***_***2***_**)****PATIENT:** Four measurement points, if possible: 8 days preoperative (t_1_), 1 day preoperative (t_2_), 6 months postoperative (t_3_), and 1 year postoperative (t_4_).

**Fig 1 pone.0328528.g001:**
[figure not shown]
SPIRIT schedule: t1 = 7 days before t2; t2  = 1 day before surgery; t3 = 6 months after surgery; t4 = 1 year after surgery.

5**Outcome Parameters:** The following EMG parameters will be recorded for all specified muscles:▫**MVIC:** The highest EMG activity within a defined period of 250ms during maximum voluntary isometric muscle contraction.▫**EMG LV:** Average EMG activity during slow (30°/s) passive stretch within a defined period (starting 200ms prior reaching maximum stretching velocity until 90% of the maximal range of motion is achieved [12]).▫**EMG HV**: Average EMG activity during fast (180°/s) passive stretch within a defined period (starting 200ms prior reaching maximum stretching velocity until 90% of the maximal range of motion is achieved [12]).**EMGchange:** EMG HV - EMG LV [12].6
**Covariates:**
▫**Angular Velocity** (calculated from 3D motion analysis)▫**Acceleration** (calculated from 3D motion analysis)

### Sample size calculation

Based on our preliminary work, the following effect size and resulting sample size were calculated for the primary outcome parameter, EMGchange, during passive stretch of the biceps brachii in patients with elbow flexor spasticity (one-sided, α = 0.05, power (1–β) = 0.8) compared to healthy participants. (Table 1)

**Table 1 pone.0328528.t001:** Sample size calculation based on the primary outcome parameter (EMGchange (%MVIC)); SD = standard deviation.

Parameter	Mean (patient)	SD (patient)	Mean (healthy)	SD (healthy)	Effect Size	Sample Size per group
EMGchange	19.1	21.1	0.04	0.1	0.91	10

The sample size calculation for the pre-/post-surgical comparison is based on our preliminary data. In a group of 7 patients with elbow flexor spasticity who underwent hyperselective neurectomy (HSN) of the elbow flexors as a surgical treatment, we were able to perform objective spasticity testing of the elbow. For the primary outcome parameter, EMGchange, the following effect size and resulting sample size were determined (one-sided, α = 0.05, power (1-β) = 0.8) (Table 2):

**Table 2 pone.0328528.t002:** Sample size calculation for a pre-/post-analysis based on the primary outcome parameter (EMGchange (%MVIC)) in 7 patients with elbow flexor spasticity who underwent hyperselective neurectomy (HSN) of the elbow flexors; SD = standard deviation.

Parameter	Mean preop	SD preop	Mean postop	SD postop	Effect Size	Sample Size
EMGchange (n = 7)	21.7	23.7	7.4	4.2	0.65	16

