After analyzing the preoperative and 6 months postoperative measurements from a minimum of 15 patients, a first interim analysis will be conducted using a paired two-sample t-test to determine any significant changes in the defined outcome parameters (EMG LV, EMG HV, EMGchange, extension deficit for wrist flexors (FCR, FCU), and finger flexors (FPL, FDP, and FDS)). If normal distribution is not confirmed, the Wilcoxon test will be applied.

Upon completion of all postoperative measurements, changes in the defined outcome parameters (EMG LV, EMG HV, EMGchange, extension deficit for wrist flexors (FCR, FCU), and finger flexors (FPL, FDP, and FDS)) across the three measurements (preoperative, 6 months postoperative, 1 year postoperative) will be examined using one-way repeated measures ANOVA. If histogram analysis and the Kolmogorov-Smirnov test indicate that the data are not normally distributed, the Friedman test will be used as a non-parametric alternative to ANOVA for comparing the three measurements.

The significance level α is set at 0.05. For significant differences, a post hoc paired t-test will be conducted, with α adjusted for multiple testing using the Bonferroni-Holm correction.

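### The pre/post sample size of 16 has 80% power only for one one-sided paired t-test, not for the non-directional, Holm-adjusted tests that the analysis section plans

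*Protocol article*

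**What the plan says.** Under Sample size calculation, the pre/post comparison rests on one parameter and one test: "the following effect size and resulting sample size were determined (one-sided, α = 0.05, power (1-β) = 0.8". The Table 2 row reads "EMGchange (n = 7) 21.7 23.7 7.4 4.2 0.65 16": preoperative mean and SD, postoperative mean and SD, effect size, and sample size. The text and the table caption both give the source of the effect size as seven patients with elbow flexor spasticity treated by hyperselective neurectomy.

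Under Statistical analysis, the pre/post testing has three parts:

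- **Interim.** Once 6-month data are available "from a minimum of 15 patients, a first interim analysis will be conducted using a paired two-sample t-test to determine any significant changes". The Wilcoxon test replaces the t-test if normality fails.
- **Final, first step.** The outcome parameters "across the three measurements (preoperative, 6 months postoperative, 1 year postoperative) will be examined using one-way repeated measures ANOVA", or the Friedman test if normality fails.
- **Final, second step.** Where the first step is significant, paired t-tests follow, "with α adjusted for multiple testing using the Bonferroni-Holm correction".

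The significance level is 0.05. The section does not say that any of these tests is one-sided.

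**The concern.** A sample size supports a power claim only for the test it was calculated for. Table 2 is calculated for one directional comparison of two time points at the full 0.05. The final analysis first asks a question without direction across three time points. It then compares pairs of time points at a reduced alpha. No calculation is given for either step.

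Sub-hypothesis d is that the method can measure postoperative improvement. The preoperative to 6-month change in EMGchange is the contrast that Table 2 appears to size. If its real power is well below 80%, a non-significant result could be read as evidence against the method when the study was simply too small for the test it used.

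**Working it through.** **Inputs.** From Table 2: means 21.7 and 7.4, SDs 23.7 and 4.2, effect size dz = 0.65, n = 16. From the text: one-sided alpha 0.05 and power 0.80. From Statistical analysis: interim minimum 15, analysis alpha 0.05, three time points (hence three pairwise comparisons), Holm.

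**Reading the effect size.** The mean difference is 21.7 − 7.4 = 14.3. A dz of 0.65 implies an SD of differences of 14.3 / 0.65 = 22.0. The implied pre/post correlation is (23.7² + 4.2² − 22.0²) / (2 × 23.7 × 4.2) = 95.33 / 199.08 = 0.48. So 0.65 is a plausible paired effect size.

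**Formula.** For a paired t-test, power = P(T > c), where T is noncentral t with n − 1 degrees of freedom and noncentrality dz√n, and c is the critical value. A two-sided test adds the negligible lower tail.

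**Reproducing the plan.** At n = 16 the noncentrality is 0.65 × 4 = 2.60. One-sided at 0.05, c = 1.753 and power is 79.8%. At dz = 0.650 exactly, 17 patients are needed to pass 80%. At 0.653, which also rounds to 0.65, 16 suffice. Table 2 is correct for its own inputs.

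**Other paired tests at the same effect size.**

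| n | one-sided 0.05 | two-sided 0.05 | two-sided 0.05/3 (first Holm step) |
|---|---|---|---|
| 15 (interim minimum) | 77.3% | 64.9% | not a planned test |
| 16 | 79.8% | 68.1% | 48.3% |
| 20 | 87.6% | 78.7% | 61.5% |
| 21 | 89.1% | 80.9% | 64.4% |
| 28 | 95.6% | 91.2% | 80.5% |

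At n = 16 the two-sided critical value is 2.131 and the first-step Holm value is 2.694, against the same noncentrality of 2.60. Reaching 80% takes 21 patients two-sided and 28 at the first Holm step. Over the rounding range of dz (0.645 to 0.655), two-sided power at n = 16 is 67.5% to 68.8%.

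**The final sequence.** The first Holm step is the worst case, because later steps use a larger alpha. The whole sequence was therefore simulated: ANOVA at 0.05, then Holm over three pairs, counting rejections for preoperative versus 6 months. The assumptions are normal data, Table 2 means and SDs, pre/post correlation 0.48 to 0.50, 12-month mean and SD equal to the 6-month values, and correlation 0.5 between the two postoperative visits. The document gives none of the 12-month inputs.

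- Preoperative versus 6 months after ANOVA and Holm: about 50 to 52% at n = 16, 64% at n = 20, 82% at n = 28.
- ANOVA alone, no sphericity correction: about 78% at n = 16 and 86% at n = 20.
- ANOVA alone, conservative (lower-bound) sphericity correction: about 68% at n = 16.

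**The case against.** Several points on the other side stand and limit the finding.

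- **Table 2 contains no arithmetic error.** A reader might infer one, but 16 follows from the stated inputs. The fault lies between two sections.
- **The interim test is not stated to be two-sided.** The plan speaks of a test "using a paired two-sample t-test to determine any significant changes in the defined outcome parameters". That wording can mean change in either direction, or change in any of the listed parameters. The sample size section declares one-sided testing and sub-hypothesis d is directional, so a one-sided interim test is compatible with the text. Its power at 15 would then be 77%, little below target.
- **Fifteen is a floor for an interim look, not the final sample.** Starting an interim look below 16 is not in itself a contradiction. A reader might also combine the 15 patients with the Holm reduction, but Holm applies only to the tests after the final ANOVA, so no planned test carries both.
- **The first-line final test loses little if left uncorrected.** The large loss falls on the pairwise contrast, and its simulated size depends on assumed 12-month values.
- **The origin of the effect size is not concealed.** The article says that it comes from "In a group of 7 patients with elbow flexor spasticity" and repeats this in the table caption. There is no disclosure to ask for.

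None of this removes the mismatch. ANOVA and Friedman have no direction whatever was intended for the interim test, and the pairwise tests that would identify a preoperative to 6-month change are run at a reduced alpha.

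**Conclusion.** The concern holds as an inconsistency between the sample size and the planned analysis, and it should be fixed. The 80% claim is true for one one-sided paired t-test of EMGchange on 16 patients. In the final analysis the same contrast has about 50 to 52% power at n = 16, or 48% at the first Holm step. A single unadjusted two-sided test would have 68%. If the planned effect is real, it would be missed about one time in two in the first case and one time in three in the second.

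The paired-test figures rest only on dz = 0.65. The 50 to 52% also rests on the assumed 12-month values and postoperative correlation.

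A reader might take the 20 patients named under Statistical analysis as cover for the shortfall. The document does not support that. Those 20 are for the reliability part, and postoperative visits take place only if surgery is performed. Power at 20 is therefore conditional on 20 patients providing pre/post data.

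**What to change.** - Name EMGchange, preoperative versus 6 months, as the one primary pre/post contrast. Test it once at 0.05 on all patients with a 6-month visit. Make the ANOVA or Friedman analysis, the Holm-adjusted pairwise tests and the other parameters secondary.
- State the sidedness of that test. If two-sided, restate the power as 68% at 16 patients and, only if 20 provide pre/post data, 79%. The effect sizes detectable with 80% power are then dz = 0.75 and 0.66. If one-sided, prespecify and justify it in the analysis section, so that Table 2 and the analysis agree.
- If the Holm-adjusted pairwise tests are to carry the conclusion instead, give a calculation for them. At dz = 0.65 it leads to about 28 patients.

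Under the first two items the cost is wording and restated figures. No extra patients are required, but a two-sided test means a less favourable stated power.

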### Statistical analysis

To determine the reliability of the proposed instrumented assessment protocol, a total of 20 patients with spasticity will be included. These patients must not have undergone prior surgery distal to the elbow and must not have received botulinum toxin injections within the past 6 months. A preoperative measurement will be conducted twice for each patient within 1 week to assess the repeatability (test-retest reliability) of the proposed assessment. By correlating the outcome parameters of the two measurement time points, the Intraclass Correlation Coefficient (ICC, interval-scaled data) will be calculated. Similarly, the ICC for healthy participants will be calculated based on the two measurements 1 week apart. The inter-rater reliability will be determined for healthy participants and for patients with spasticity using the measurement at the first time point each. For this purpose, all spasticity assessments will be conducted by two trained examiners. The ICC will then be calculated by correlating the outcome parameters. Standard Error of Measurement (SEM) and Minimal Detectable Difference (MDD) will be reported.

The 20 arms of the healthy participants may include both arms from the same individual. However, measurements will be performed on two separate days. We assume that each arm functions independently without influencing the other side and therefore treat all arms as independent samples, regardless of whether data from both arms of a single participant are included.

A validity analysis in the strict sense is not possible for the proposed methodology, as there is currently no non-invasive valid measurement technique for assessing spasticity. Alternatively, in clinical practice, the subjective scales MAS and TS are used with moderate reliability. Accordingly, the correlation of the determined spasticity parameters by the instrumented assessment method with both scales will be calculated. For this, the Spearman rank correlation coefficient (minimum ordinal data) will be used.

The study design concerning pre-/post treatment analysis corresponds to an experimental prospective cohort study. Initially, the normal distribution of the interval-scaled parameters will be confirmed (Kolmogorov-Smirnov test and visual inspection using histograms).

After analyzing the preoperative and 6 months postoperative measurements from a minimum of 15 patients, a first interim analysis will be conducted using a paired two-sample t-test to determine any significant changes in the defined outcome parameters (EMG LV, EMG HV, EMGchange, extension deficit for wrist flexors (FCR, FCU), and finger flexors (FPL, FDP, and FDS)). If normal distribution is not confirmed, the Wilcoxon test will be applied.

Upon completion of all postoperative measurements, changes in the defined outcome parameters (EMG LV, EMG HV, EMGchange, extension deficit for wrist flexors (FCR, FCU), and finger flexors (FPL, FDP, and FDS)) across the three measurements (preoperative, 6 months postoperative, 1 year postoperative) will be examined using one-way repeated measures ANOVA. If histogram analysis and the Kolmogorov-Smirnov test indicate that the data are not normally distributed, the Friedman test will be used as a non-parametric alternative to ANOVA for comparing the three measurements.

The significance level α is set at 0.05. For significant differences, a post hoc paired t-test will be conducted, with α adjusted for multiple testing using the Bonferroni-Holm correction.

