### Participants

**Healthy Participants**: 20 arms of healthy participants will be recruited for baseline measurements.

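### Two arms of one healthy person are analysed as independent samples, so the stated precision of the healthy-group results is too high whenever both arms are used

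*Protocol article*

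**What the plan says.** Under Participants, the healthy sample is set in arms, not people: "20 arms of healthy participants will be recruited for baseline measurements". Under Statistical analysis, "The 20 arms of the healthy participants may include both arms from the same individual". The number of people can thus lie anywhere from 10 to 20.

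The same section gives the justification, "We assume that each arm functions independently without influencing the other side", with the remark "However, measurements will be performed on two separate days". The resulting analysis rule is that the authors "therefore treat all arms as independent samples, regardless of whether data from both arms of a single participant are included".

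These arms feed several healthy-group results in that section:

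- Test-retest: "Similarly, the ICC for healthy participants will be calculated based on the two measurements 1 week apart".
- Inter-rater: "The inter-rater reliability will be determined for healthy participants and for patients with spasticity using the measurement at the first time point each".
- Error measures: "Standard Error of Measurement (SEM) and Minimal Detectable Difference (MDD) will be reported".

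The article describes no adjustment for person.

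**The concern.** The justification confuses two ideas. One arm may have no effect on the other, and the two may still give correlated values because they belong to the same person. They share age, sex, build, tissue properties, the ability to relax and the effort put into the maximum voluntary contraction. That last item matters directly, because the Equipment section normalises the EMG signals to it.

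Separate days can reduce error that is shared within a session, but they cannot remove traits that the person carries from day to day. The remark about days is also ambiguous. The Detailed work plan already gives healthy participants two sessions 7 days apart. If those are the days meant, both arms could be measured in the same sessions and share session error as well.

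This is a stated analysis rule, not a detail left to a fuller document. What is at stake is the precision claimed for the healthy part of sub-hypothesis b (reliable measurement): results could be presented as resting on 20 independent units when as few as 10 people were measured.

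**Working it through.** **The plan's own figure.** The only sample-size calculation that involves healthy participants is Table 1: patient mean 19.1 (SD 21.1), healthy mean 0.04 (SD 0.1), one-sided α 0.05, power 0.80, 10 per group. With the healthy SD close to zero, the standardised difference is (19.1 − 0.04)/21.1 = 0.903. An unequal-variance t-test then behaves like a one-sample test with n − 1 degrees of freedom, which gives n = 10 (power 0.838). The stated 10 is reproduced. No calculation is given for the 20 arms or for the reliability analysis.

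**Healthy mean.** Inputs: 20 arms (Participants); b people giving both arms (not stated); between-arm correlation ρ (not stated, so assumed). The variance of the mean is σ²(20 + 2bρ)/400, so effective n = 400/(20 + 2bρ). For b = 10 this reduces to 20/(1 + ρ). The SE relative to σ/√20 is √(20/effective n).

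| ρ (assumed) | Effective n, 10 people × 2 arms | SE ratio | Effective n, 5 bilateral + 10 single | SE ratio |
|---|---|---|---|---|
| 0 | 20.0 | 1.00 | 20.0 | 1.00 |
| 0.2 | 16.7 | 1.10 | 18.2 | 1.05 |
| 0.5 | 13.3 | 1.22 | 16.0 | 1.12 |
| 0.8 | 11.1 | 1.34 | 14.3 | 1.18 |

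**ICC, SEM and mean by simulation.** 40,000 runs of 10 people × 2 arms × 2 sessions, total variance 1, true ICC 0.75, one-way ICC with its usual F-based 95% interval, and a t interval for the mean of one session, all computed as if the 20 arms were independent.

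| Between-arm correlation: true score / session error | Mean ICC | ICC interval coverage | Mean SEM (sampling SD) | Coverage for the mean |
|---|---|---|---|---|
| 0 / 0 | 0.731 | 95.0% | 0.494 (0.079) | 95.1% |
| 0.5 / 0 | 0.723 | 93.9% | 0.494 (0.079) | 90.6% |
| 0.8 / 0 | 0.714 | 92.0% | 0.493 (0.078) | 87.4% |
| 0.8 / 0.8 | 0.710 | 87.6% | 0.490 (0.099) | 84.6% |

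The mean ICC falls by at most 0.021 (0.731 to 0.710) and the SEM by 0.004. The sampling SD of the SEM grows only when session errors are shared (0.079 to 0.099). For SEM, and for MDD as a multiple of it, correlation in the errors is therefore what costs precision. The inter-rater ICC has the same layout, 20 arms with two values each, so these figures are a guide to it too.

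**Patient versus healthy.** Using the Table 1 SDs with 20 patients and 20 arms from 10 people, the SE of the difference is √(21.1²/20 + 0.1²(1 + ρ)/20). At ρ = 0 it is √(22.2605 + 0.0005) = 4.71816; at ρ = 1 it is √(22.2605 + 0.0010) = 4.71821. The increase is about 0.001%.

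**The case against.** The defence has four good arguments.

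- The assumption is disclosed openly, and the text says only that both arms may be included. If every arm comes from a different person, or ρ is 0, nothing is overstated. This stands as a limit on size, but the plan guarantees neither condition.
- The article names ICC, SEM and MDD but no confidence interval and no SE of a healthy mean. The quantities it does name are nearly unchanged as point estimates. This stands: the point concerns whatever precision is attached to them, including the implied sample of 20.
- If the separate days mean one day per arm, shared session error is the part that would shrink, and ICC coverage stays at 92% to 94%. This is a fair reading, but the text does not settle it.
- The healthy arms do not enter the patient ICC, the pre/post tests or the repeated-measures ANOVA, nor the correlations with MAS and TS in so far as these concern spasticity. This stands.

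A reader might also infer that the patient-versus-healthy comparison becomes anti-conservative. The document's own figures do not support that: with healthy SD 0.1 against patient SD 21.1, the healthy group adds almost nothing to the standard error, and even 10 people meet the 10 per group of Table 1. Those SDs come from elbow pilot data, but they are the only ones given.

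**Conclusion.** The independence rule is wrong as written, and nothing else in the article corrects it. The consequence is confined to the precision of healthy-group results: intervals for the ICC and the baseline mean, and for SEM and MDD where session errors are shared between arms.

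For a healthy mean, effective n is 16.7 to 11.1 if 10 people give both arms, and 18.2 to 14.3 if 5 do, for ρ from 0.2 to 0.8. The loss for ICC intervals is modest (about 94% to 92% coverage at true-score correlations of 0.5 to 0.8) unless session errors are shared too, when it reaches about 88%. All of this rests on an assumed ρ, and the coverage figures also on every person being bilateral and a true ICC of 0.75.

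It would be tempting to conclude that the healthy ICC, SEM and MDD are themselves biased or that the study's main comparisons are compromised. The calculations do not support either. This should be fixed, but it does not threaten the patient results.

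**What to change.** Delete the statement that arms are independent. Report the number of healthy people and the number who contributed both arms alongside the 20 arms, and state whether the separate days refer to the two arms or to the two test sessions.

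Compute healthy-group intervals for ICC, SEM, MDD and means from a mixed model with arm nested in person, or by a bootstrap that resamples people and keeps both arms of a person together.

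This needs no new data: a change of wording and a few lines of analysis code. The downside is slightly wider healthy-group intervals.

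### EMGchange is named primary but gets no priority or primary muscle in the analysis: 15 EMG cells are each tested at α = 0.05, with Holm apparently covering only visit pairs

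*Protocol article*

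**What the plan says.** All references are to the protocol article.

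- **Primary outcome.** The sample size section gives figures "calculated for the primary outcome parameter, EMGchange", one-sided at α = 0.05 with power 0.8. They come from preliminary data on the elbow flexors, so they do not identify a wrist or finger muscle.
- **What is recorded.** Under the outcome parameters in the detailed work plan: "The following EMG parameters will be recorded for all specified muscles". EMGchange is defined there as EMG HV minus EMG LV.
- **What is tested.** The statistical analysis section sets out "to determine any significant changes in the defined outcome parameters (EMG LV, EMG HV, EMGchange, extension deficit for wrist flexors (FCR, FCU"). Three finger flexors complete the list: FPL, FDP and FDS.
- **When.** After at least 15 patients have 6-month data, "a first interim analysis will be conducted using a paired two-sample t-test to determine any significant changes in the defined outcome parameters". At the end, the same parameters ("preoperative, 6 months postoperative, 1 year postoperative) will be examined using one-way repeated measures ANOVA") are tested again. Wilcoxon and Friedman tests are the non-parametric alternatives.
- **Error control.** One level is given: "The significance level α is set at 0.05". The only correction mentioned comes after a significant result: "For significant differences, a post hoc paired t-test will be conducted, with α adjusted for multiple testing using the Bonferroni-Holm correction".

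The statistical analysis section does not single out EMGchange, choose a muscle or a visit, state sidedness, or allot any α to the interim.

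**The concern.** Holm enters only after an omnibus result has been declared significant at 0.05. It therefore does not protect against the number of muscles and parameters searched. The three EMG parameters are also linked by definition, so significance in two of them is not independent corroboration.

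This is more than detail left to an analysis plan. The article itself states the tests, the α and the place where the correction applies. The primary label in the sample size section has no counterpart in the analysis.

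At stake is hypothesis (d), that the method can measure improvement after surgery. No passage says which result would support or refute it. An isolated favourable cell could then be presented as support, in a project that aims to inform surgical decisions and quality control.

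**Working it through.** **1. The plan's own figure.** Table 2 gives d = 0.65 and n = 16 for a paired, one-sided test at 0.05. The noncentrality is 0.65 × √16 = 2.6 on 15 degrees of freedom, which gives power 0.798. Reaching 0.80 exactly takes n = 17, so 16 is reproduced to within rounding. This is the sample size for one test of one outcome.

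**2. Number of cells.** 3 EMG parameters × 5 muscles (FCR, FCU, FPL, FDP, FDS) = 15. Extension deficit adds between 2 (wrist, finger) and 5 (one per muscle), giving 17 to 20. The article does not fix this count, so the range is an assumption.

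**3. Independence formula.** The chance of at least one false positive is 1 − (1 − 0.05)^k:

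- k = 5: 1 − 0.95^5 = 22.6%
- k = 15: 1 − 0.95^15 = 53.7%
- k = 20: 1 − 0.95^20 = 64.2%

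The last two cannot apply here. EMGchange = HV − LV cannot be uncorrelated with both of its components, so the 15 cells are never independent.

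**4. Simulation with the identity built in.** Assumptions: no true change in any cell, n = 16, one look, paired t-tests at two-sided 0.05, normal differences, LV–HV correlation 0 to 0.8. The results move by a point or two with the LV–HV correlation.

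| Between-muscle correlation | 15 cells: any false change | 15 cells: false improvement | EMGchange, 5 muscles: any | EMGchange, 5 muscles: improvement |
|---|---|---|---|---|
| 0 | up to 49% | about 29% | about 23% | about 12% |
| 0.5 | 39–41% | 22–23% | about 19% | about 9% |
| 0.8 | about 28–30% | about 16% | about 13% | about 7% |

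If EMGchange is tested one-sided at 0.05, as in the sample size section, false improvement over the five muscles is about 12–23%.

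**5. The interim, for a single outcome.** Assumptions: interim at 15 patients, final at 16 or 20, between-visit correlation 0.5, two-sided. The final pairwise comparison is made as planned, only after a significant ANOVA and with Holm.

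- False preoperative-versus-6-month claim at either look: 5.0–5.3%.
- If the final omnibus result also counts as a claim: 7.9–8.3%.
- For comparison, repeating the same unadjusted paired test at both looks would give 6.2–7.4%, but that is not the plan.

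**6. Price of a Holm correction over five muscles.** The first step uses α = 0.05/5 = 0.01. At d = 0.65, n = 16, one-sided, power falls from 0.80 to about 0.52. Restoring 0.80 at that step takes 27 patients one-sided or 32 two-sided.

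**The case against.** **EMGchange is named as primary, so the key family is five tests.** This is fair, and it lowers the error considerably. But the analysis section does not use the label and names no muscle. Even the five-muscle family has a 13–23% chance of some false significant change.

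**The Holm family is not spelled out, and an unseen analysis plan may define it.** This is possible. Restriction to visit pairs is the natural reading of a correction attached to post hoc paired tests, but it is an inference. If a wider family was meant, one sentence would settle it.

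Stronger readings that a reader might infer, and why the documents do not support them:

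- *A false improvement is more likely than not.* The 54% and 64% figures need independent cells and count worsening as well. Even with the interim and final analyses combined, 17 or 20 cells, and 20 patients assumed at the end, false improvement is 25–44% with two-sided tests. Only one-sided testing with low correlation passes 50% (33–60% at an interim tested one-sided at 0.05), and the analysis section states no sidedness. The limitations section expects substantial cross-talk between forearm muscles, which plausibly pushes correlation up.
- *Any one significant cell would confirm hypothesis (d).* No passage says so. The defect is that no decision rule is given.
- *The interim seriously inflates the error.* No stopping rule is tied to it, and the planned ANOVA-plus-Holm route keeps the pairwise claim near 5%.

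It also stands that this is an observational, single-centre study developing a measurement method, and that a complete absence of change after surgery is a worst case.

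**Conclusion.** The point holds at a moderate size and is a should-fix. The stated rules test 15 EMG cells (17 to 20 with extension deficit) at an undivided 0.05, twice, and the named primary outcome has no protected place among them. For one analysis of the EMG cells, the chance of at least one false significant change is about 28–49%, and of a false improvement about 16–29%. The main inflation comes from the number of cells. The interim contributes little unless the omnibus result is itself treated as a claim, in which case the error for one outcome is about 8%.

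These rates assume no true change anywhere, two-sided tests, n = 16 and between-muscle correlation from 0.8 down to 0. The document gives no correlations, so the range is the result.

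**What to change.** 1. State one confirmatory EMGchange value per patient, for example the mean over the flexors operated on, with its visit and sidedness.
2. Label EMG LV, EMG HV, extension deficit and all muscle-level results as secondary or exploratory, reported with confidence intervals.
3. Make the interim descriptive, without significance claims.
4. State which comparisons the Holm correction covers.

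**Cost.** No extra measurements are needed. Fewer results can be called significant, and an averaged primary describes overall flexor change, not each muscle.

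The alternative, Holm over the five muscles for EMGchange, keeps muscle-level claims but is not a change of wording only. The power statement would have to be redone: about 0.52 at the first step with 16 patients (d = 0.65, one-sided).
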